## Abstract

**Background:**

The Southeastern United States has the lowest kidney transplant rates in the nation, and racial disparities in kidney transplant access are concentrated in this region. The Southeastern Kidney Transplant Coalition (SEKTC) of Georgia, North Carolina, and South Carolina is an academic and community partnership that was formed with the mission to improve access to kidney transplantation and reduce disparities among African American (AA) end stage renal disease (ESRD) patients in the Southeastern United States.

**Methods/Design:**

We describe the community-based participatory research (CBPR) process utilized in planning the *R*educing *D*isparities *I*n *A*ccess to kid*N*ey *T*ransplantation (RaDIANT) Community Study, a trial developed by the SEKTC to reduce health disparities in access to kidney transplantation among AA ESRD patients in Georgia, the state with the lowest kidney transplant rates in the nation. The SEKTC Coalition conducted a needs assessment of the ESRD population in the Southeast and used results to develop a multicomponent, dialysis facility-randomized, quality improvement intervention to improve transplant access among dialysis facilities in GA. A total of 134 dialysis facilities are randomized to receive either: (1) standard of care or “usual” transplant education, or (2) the multicomponent intervention consisting of transplant education and engagement activities targeting dialysis facility leadership, staff, and patients within dialysis facilities. The primary outcome is change in facility-level referral for kidney transplantation from baseline to 12 months; the secondary outcome is reduction in racial disparity in transplant referral.

**Discussion:**

The RaDIANT Community Study aims to improve equity in access to kidney transplantation for ESRD patients in the Southeast.

**Trial registration:**

Clinicaltrials.gov number NCT02092727.

## Background

For the majority of the more than 600,000 patients in the United States (US) with end stage renal disease (ESRD) [1], kidney transplantation is the preferred treatment, providing longer survival, better quality of life, lower hospitalization rates, and substantial cost savings compared to dialysis [2, 3]. Despite these benefits, kidney transplantation is not available to all ESRD patients due to the paucity of available organs as well as long-standing racial disparities in access to both living donor (LD) and deceased donor (DD) transplantation [4–7]. Racial disparities in kidney transplant access are concentrated in the Southeastern US [4, 6, 8], where African American (AA) patients represent 67% of the prevalent ESRD population and where LD and DD transplant rates are the lowest in the nation [9, 10]. Targeting the ESRD regions with the most racial disparity in access to kidney transplantation could reduce the overall racial disparity in access to kidney transplantation [11]. However, despite numerous studies showing consistent racial disparities in access to transplantation, few interventions have been implemented to reduce disparities in the transplant process [12].

Our Southeastern Kidney Transplant Coalition (SEKTC) was formed in 2010 with the help of ESRD Network 6 (Southeastern Kidney Council) with a mission of improving equity in access to kidney transplantation for ESRD patients in the Southeast, particularly Georgia (GA), North Carolina (NC), and South Carolina (SC). This group consists of voluntary stakeholders in the ESRD community, including ESRD patients, dialysis facilities, transplant centers, social workers, organ procurement organizations, healthcare providers, academic researchers, patient advocacy groups within the tri-state region, and ESRD Network 6 staff.

At our inaugural SEKTC face-to-face meeting in February 2011, our SEKTC partners utilized a standard quality improvement approach to discuss root causes of delayed access to kidney transplantation in the Southeast to help inform the development of a multicomponent, quality improvement intervention [13]. A variety of patient-, provider-, dialysis facility-, neighborhood-, and health systems-level factors were identified as major barriers for the primarily AA ESRD patient population in the Southeast. These included: patient factors, such as lower income [14, 15], education [5], access to healthcare [16], education [5], medical comorbidities [17, 18], low health literacy [19], cultural beliefs and patient preferences [20–27], and limited social networks [28–30]; provider factors, such as misconceptions that AA patients do better on dialysis compared to transplant [23, 31–36], lack of education about kidney disease and the transplant process [37, 38], lack of information about the risks and benefits of treatment options among both patients and providers [31, 32], and provider bias [39–41]; and system-level factors, such as policies resulting in delays in access or outcomes on the basis of race, ethnicity, or socioeconomic status and non-standardized requirements for patient-provider discussions about transplantation [42].

The SEKTC members recognized significant gaps in our knowledge about the reasons for low kidney transplantation rates among AA ESRD patients in the Southeastern region. Our primary limitation was the lack of surveillance data on key steps in the transplantation process including lack of information on providers generating transplant referrals, provider perceptions on kidney transplantation, and patient-reported barriers to transplantation in the Southeast. Coalition members formed subgroup committees to address these gaps and, throughout the following 18 months, performed qualitative and quantitative research to improve our understanding of the challenges within the transplantation process in the Southeast. Detailed results from this population needs assessment [43–46] are described elsewhere, but we describe these results in brief below since these results influenced the development of multi-component intervention activities for the Reducing Disparities In Access to kidNey Transplantation (RaDIANT) Community Study.

Quantitative analyses of the Dialysis Facility Report data revealed significant variability in transplant rates across dialysis units in Network 6, where 80% of dialysis facilities were performing below the national average. Among the three states in ESRD Network 6, GA had the lowest kidney transplant rates, which were also the lowest rates in the entire nation [9]. Other quantitative analysis involved data from a dialysis-facility survey administered through our community partners. Results from this survey of more than 500 dialysis facility providers in GA, NC, and SC found that almost all providers (98.4%) reported they were comfortable discussing kidney transplantation with patients. However, most staff reported that >50% of their patients were not interested in transplantation [44]. Approximately 30% of providers believed that they did not have sufficient training about transplantation and did not have sufficient patient educational resources (33%) [44]. Qualitative research involved focus groups conducted among 40 ESRD patients from GA, NC, and SC. Most patients were interested in kidney transplantation, although many patients were confused about the kidney transplantation process. Common patient barriers derived from these focus groups included financial concerns, medical barriers, limited social network of transplant successes, and lack of information and education on transplantation within the dialysis facility [43].

The results of this population needs assessment helped our SEKTC partners to develop the multicomponent intervention activities. Specifically, the quantitative analyses that identified GA as the state with the lowest kidney transplant rates motivated our SEKTC to focus intervention activities within GA. In addition, the extreme variability in kidney transplantation across dialysis facilities suggested the need for traditional quality improvement methods for low performing dialysis facilities, including facility protocols to ensure best practices for kidney transplant referral. Dialysis facility surveys showed that targeted education among dialysis facility staff was needed, based on staff survey results showing that a third of providers felt they did not have sufficient patient educational resources and did not have sufficient training about transplantation. Focus group analyses suggested that patients had limited knowledge about the kidney transplant process and few educational resources or tools to help clarify misinformation or lacking information.

The results of this needs assessment, combined with practical aspects such as sustainability and feasibility, helped the SEKTC members develop a multicomponent, quality improvement intervention to deliver among dialysis facilities in order to reduce racial disparities in access to kidney transplantation. The purpose of this paper is to describe the community-based participatory research (CBPR) process used to design the protocol for the RaDIANT Community Study. The strategy and methods the SEKTC used to develop a large-scale, evidence-based, quality improvement intervention could serve as a model for other academic or community partnerships in developing and implementing interventions on the ESRD Network level.

## Methods

### Study overview

The RaDIANT Community Study is a dialysis facility-level, randomized clinical trial designed to test the effectiveness of a multicomponent intervention on improving patient referral for kidney transplantation within dialysis facilities. Prior to initiation of intervention activities, the RaDIANT Community Study was registered on clinicaltrials.gov (Protocol #NCT02092727). This study was approved by Institutional Review Boards at Emory Transplant Center, Georgia Regents Kidney and Pancreas Transplant Program, and Piedmont Transplant Institute for the collection of retrospective patient referral data, but no patient contact was made between researchers and patients.

### Target population, setting, and inclusion/exclusion criteria

Under the direction of Centers for Medicare & Medicaid Services (CMS), 18 regional ESRD Networks are responsible for the quality of care of patients with kidney disease in the US. ESRD Network 6 (GA, NC, and SC) has the largest ESRD patient population among the US ESRD Networks, servicing more than 600 dialysis facilities that treat ~40,000 patients. Approximately 47% of the dialysis facilities in ESRD Network 6 are located in GA, and these facilities treated more than 12,000 dialysis patients in 2012 [47]. The RaDIANT Community Study aims to target 134 outpatient dialysis facilities in GA, representing nearly half (47%) of all GA dialysis facilities.

All dialysis facilities within GA were considered for randomization of the intervention (n = 283). To ensure that each facility had a large enough population to detect a change in the main effect of disparity reduction, facilities with a 2012 population of <25 patients (18-69 years of age) were excluded from the potential pool of facilities (n = 11). The remaining facilities were selected in a step-wise selection process: 1) The presence of a racial disparity in transplant referral (n = 75), or 2) crude annual referral in the lowest 50th percentile (referral <0.06; n = 59) for the state. The presence of a racial disparity was based on a difference of the proportion of AA ESRD patients referred and the proportion of white ESRD patients referred. The remaining facilities selected had a calculated crude referral in the lower 50th percentile. The final pool of 134 facilities were randomized by generating a random number to either the intervention (n = 67) or control (n = 67) group (Figure 1). Dialysis facilities in the intervention group are not blinded to intervention activities; however, facilities selected as controls are blinded. Researchers are not blinded to dialysis facility allocation.

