### Multicomponent intervention (Study arm 2)

Based on the results of the population needs assessment, the SEKTC aimed to develop a sustainable, multicomponent, multi-level quality improvement intervention to address disparities at the dialysis facility-, staff- and patient-level. These intervention activities were developed (or identified) by SEKTC members in face-to-face and phone conference meetings over several months. Final intervention activities were selected by the SEKTC Steering Committee members based on 1) feasibility, 2) sustainability, 3) core tenets of quality improvement interventions, and 4) perception of acceptance among stakeholders, including dialysis facilities, staff, and patients, as well as the larger kidney disease community.

The multicomponent, multi-level, quality improvement intervention targeted to dialysis facilities, staff, and patients includes educational webinars, staff- and patient-level educational activities, monthly monitoring of quality improvement activities, and traditional quality improvement oversight. Because ESRD Network 6 has significant experience with conducting large quality improvement interventions within dialysis facilities that may be performing worse than expected for a particular outcome, and because disparity reduction in transplant referral is part of the CMS Statement of Work for ESRD Networks [48], intervention activities are primarily delivered by ESRD Network 6. The ESRD Network retains the authority to mandate facility participation in quality improvement activities if deemed to have low performance; thus interventions are targeted to dialysis facilities that had either low overall kidney transplant referrals or those facilities that had a racial disparity within their facility (*i.e*., they had a lower proportion of AA vs. whites referred for kidney transplantation).

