### Outcome measures

The primary outcome of the RaDIANT Community Study is the change in facility-level transplant referral (for patients <70 years) from baseline. Baseline referral will be calculated as the average number of unique referrals in a dialysis facility over the 12-month period preceding the intervention (January-December 2013) divided by the total number of ESRD patients within the facility for that time period. Post-intervention crude referral will be measured as the average number of unique referrals generated from January-December 2014 divided by the total number of ESRD patients within the facility for the same 12 month intervention period. As described above, referral will be defined as the receipt of a referral by the transplant center. Patient-level transplant referral data with facility identifiers will be collected from all of the transplant centers in GA and aggregated to summarize the total number of referrals to any transplant center in the state divided by the total number of adult ESRD patients <70 years in the facility. If facility characteristics are not equally distributed at baseline between control and intervention groups, we will consider adjustment using a Standardized Transplantation Referral Ratio (STRR). The STRR will be defined as the total number of observed transplant referrals within a facility divided by the total number of expected referrals based on the state average and adjusting for relevant covariates, among patients aged 18–69 [similar to the Standardized Transplantation Ratio (STR) used by CMS] [1].

A secondary outcome of interest is the reduction in AA vs. white racial disparity in transplant referral. The reduction in racial disparity will be measured as the difference in the proportion of referrals among AA vs. whites. Furthermore, we will examine whether the total number of AA ESRD patients referred for transplant in the state of GA increased from baseline to 12 months to examine the absolute impact of the RaDIANT Community Study on improving access for AA ESRD patients in the state.

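### The disparity analysis could report a reduction with no AA–white gap closed: the mixed model tests AA referral alone, over a pool of 75 disparity-tier and 59 low-referral facilities

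*Protocol article*

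**What the plan says.** **Selection** (Target population, setting, and inclusion/exclusion criteria). Entry has two steps: "1) The presence of a racial disparity in transplant referral (n = 75), or 2) crude annual referral in the lowest 50th percentile", the latter being referral below 0.06 (n = 59) for the state. The second group came out of what was left after the first: "The remaining facilities selected had a calculated crude referral in the lower 50th percentile". On how disparity was judged, the section says "The presence of a racial disparity was based on a difference of the proportion of AA ESRD patients referred" and the corresponding white proportion. It gives no threshold, no minimum count and no rule for facilities where the comparison cannot be made. The direction appears only under Multicomponent intervention (Study arm 2), where disparity facilities are those where "they had a lower proportion of AA vs. whites referred for kidney transplantation".

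**Allocation** (same section as selection). "The final pool of 134 facilities were randomized by generating a random number to either the intervention" or the control group, 67 each. No stratification by entry route is stated.

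**Disparity outcome** (Outcome measures). "The reduction in racial disparity will be measured as the difference in the proportion of referrals among AA vs. whites".

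**Disparity analysis** (Statistical analyses). The two questions posed are whether the AA proportion referred rose over 12 months and whether that change differed by arm. The mixed model is described as testing the AA proportion, although the next sentence speaks of effects on referral disparity. Its terms are time, arm, their interaction and facility random effects. A separate patient-level logistic model includes an arm-by-race interaction. Neither model has a term for entry route.

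**The concern.** The secondary aim is to learn whether the intervention reduced racial disparity in referral. That requires comparing AA with white patients and showing that a shortfall shrank. Three features of the plan work against this.

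1. A model whose dependent quantity is AA referral contains no white comparator. An intervention that raises referral equally in both races gives a positive arm-by-time effect and leaves the gap where it was.
2. A signed AA–white difference keeps improving after it passes zero. A rise in AA referral above white referral scores the same as closing a deficit.
3. The facilities are a mixture. The 75 were chosen because AA patients were behind; the 59 were added for low overall referral, with no deficit identified. In a pooled signed average, a surplus in some facilities can offset a deficit in others.

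At stake is the meaning of a positive secondary result. The trial could report a smaller disparity when what it observed was a general rise in referral, or a rise in AA referral at sites where AA patients were not behind.

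**Working it through.** **1. The stated counts.** 75 + 59 = 134, which matches the randomized pool. The groups are therefore disjoint, and 59/134 = 44.0% came in through low referral.

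**2. The plan's power figure.** Inputs from Power and sample size calculations: 67 facilities per arm, 46 patients each, 14% control referral, ICC 0.01 to 0.05. Effective n per arm = 67 × 46 / (1 + 45 × ICC).
- ICC 0.01: 3082/1.45 = 2125.5; detectable difference 3.11 points (stated 3.1).
- ICC 0.05: 3082/3.25 = 948.3; detectable difference 4.76 points (stated 4.8).

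Both reproduce (two-sided 5%, 80% power), but they concern overall referral. The article gives no effect size, SD or power for the AA–white gap, so the next two steps are illustrations under assumed rates.

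**3. Equal rise in both races.** Assume AA 4% and white 8%, each rising by 4 points.
- AA-only quantity: 8 − 4 = +4 points.
- Gap before: 4 − 8 = −4. Gap after: 8 − 12 = −4. Change: 0.

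The AA-only model records 4 points; the disparity is unchanged. This could happen in any of the 134 facilities, including the 75.

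**4. AA rise where no deficit existed.** Assume a gap of −4 in the 75, 0 in the 59, equal facility weights, and a 4-point AA-only rise in the 59.
- Pooled gap before: (75 × −4 + 59 × 0)/134 = −300/134 = −2.24.
- Pooled gap after: (−300 + 59 × 4)/134 = −64/134 = −0.48.
- Shift: 59 × 4/134 = 1.76 points.

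No facility's deficit closed, and the 59 moved from parity to a 4-point gap the other way. The pooled value still moved toward zero, so a closer-to-zero rule on the pool does not by itself expose this. A display by entry tier does.

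**5. How far the entry label can be trusted.** Table 1 gives 46.6 patients per facility in the pool, 65.4% AA and 33.5% white: 30.5 AA and 15.6 white, taken as 30 and 16. Treat one year's referrals as binomial.
- Standard error of a facility's AA–white difference, √[p(1 − p)(1/30.5 + 1/15.6)]: 7.4 points at p = 6% (the selection cut-off) and 10.8 points at p = 14% (the power assumption).
- True rates equal: an apparent AA deficit arises 40% of the time at 6% and 46% at 14%.
- True rates 4% AA and 8% white (assumed): no apparent deficit 39% of the time.
- Expected white referrals at 6%: 15.6 × 0.06 = 0.94 per facility. With none, no AA deficit can appear.

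Absence of a deficit at selection is therefore weak evidence that there was none.

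**6. Chance imbalance of entry tier.** The number of disparity-tier facilities in one arm is hypergeometric (134, 75, 67). Mean 67 × 75/134 = 37.5; SD √[67 × (75/134) × (59/134) × (67/133)] = 2.88; 95% range 32 to 43. The arms differ by 7 or more such facilities with probability 0.30.

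**The case against.** The strongest reply has four parts.

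- **The mixed pool is deliberate.** The article explains why it targets either kind of facility, and the primary outcome, overall referral, suits both. This stands. A reader might infer that the primary analysis is affected. The documents do not support that: the ANCOVA compares overall referral between randomized arms and adjusts for baseline referral.
- **Nothing says the 59 lacked a deficit.** This also stands. A reader might infer that they have no disparity to reduce, but that is only an inference from step-wise selection. The rule has no stated threshold or handling of non-assessable facilities, and the small counts make the label unreliable.
- **Race is compared elsewhere.** The patient-level model tests arm by race, and predicted referral is to be compared by race within arms. This answers part of the point: a white comparator exists in the plan. But that model is introduced for the absolute increase in AA referrals. An interaction favouring AA patients is also signed, so it does not show whether a deficit shrank or a surplus grew.
- **Randomization is unbiased without stratification.** Correct. Tier imbalance costs precision only, and facility random intercepts absorb baseline level differences.

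It can also be said that raising AA referral in low-referral facilities narrows a pooled or statewide AA shortfall, which the secondary aim reaches for. That is a fair reason to keep the pooled estimate as the main result.

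**Conclusion.** The point holds in this form. As described, the disparity analysis can support a claim of reduction with no AA–white gap closed. The main cause is the mismatch between Outcome measures, which names an AA–white difference, and Statistical analyses, where the mixed model tests the AA proportion. Signed averaging over two differently selected groups of facilities adds to it.

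The size cannot be fixed from the article. The 4-point and 1.8-point figures are illustrations that rest on assumed rates and, for the second, on equal facility weights and an effect confined to the 59. The firm numbers are the 75/59 split and the 44%.

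Two stronger readings are not supported. One is that pooling dilutes the effect to 75/134 = 56%; that needs a zero disparity effect in the 59, which nothing in the article implies, and with equal effects there is no dilution. The other is that the disparity estimate should rest on the 75 alone; that changes the estimand, discards 44% of facilities and relies on a noisy label.

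**What to change.** 1. Make the AA–white gap the dependent quantity of the disparity model, or use race × arm × time, so that Statistical analyses matches Outcome measures. Report AA referral alone as a separate access result, not as disparity.
2. State that a claim of reduction requires the gap in the intervention arm to be closer to zero than in control, not merely more favourable to AA patients.
3. Keep the pooled 134-facility estimate as the main disparity result. As supportive, report the arm contrast within each entry tier, with a tier-by-arm term. Use between-arm contrasts rather than before–after changes by tier: facilities selected on a noisy deficit will tend to drift back toward the average in both arms.

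**Cost.** Wording in the analysis plan only. Entry tier is known for every facility, and race is among the patient-level referral data already collected. The downside is limited precision within tiers. With equal SDs, standard errors are √(134/75) = 1.34 and √(134/59) = 1.51 times the pooled one. The standard error of the difference between tier effects is √[134 × (1/75 + 1/59)] = 2.01 times the pooled one. The tier results should therefore be read as description and not as separate tests.
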